#### Economic evaluation

The economic evaluation will be performed alongside the clinical trial. The economic evaluation will be designed as a cost-effectiveness analysis of the addition of IUI, use of gonadotrophins or the combination of both as compared to CC alone, with the costs per singleton pregnancy within eight months after randomisation resulting in live birth as the primary outcome measure. We will also assess the time to a successful pregnancy in the cost-effectiveness analysis. In this analysis, costs and effects will be discounted for 4% per year.

### Determining costs

The economic analysis will be performed from a societal perspective. A distinction will be made between costs of medical interventions (direct costs) and costs resulting from productivity losses (indirect or time costs). Standardised unit costs will be calculated for all centres based on actual expenses made during the study. Subsequently, unit costs will be applied to resource use as observed in participating centres. Resource utilisation will be documented using individual patient data in the CRF’s. Detailed information on complications will be obtained. Resource unit prices will reflect the unit of staff, materials, equipment, housing, depreciation and overhead. Productivity loss will be valued using Dutch reference data (hand book of the Dutch health council). Costs will be presented in Euros.

For each cost category, costs are measured as the volumes of resources used multiplied with appropriate valuations (unit-costs). Unit costs will be estimated according to the Dutch guideline on (unit) costing in health care (Oostenbrink, Bouwmans etal., 2004). Visits to GPs, medical specialists and paramedical care, and travelling will be valued based on the guideline prices. The friction cost method will be used to estimate the duration of lost productivity, age adjusted average daily wages will be used to value this duration. An analysis based on reimbursement fees is added (insurer perspective). Study-specific costs are excluded from analysis.

### Cost-effectiveness analysis

Cost-effectiveness of each strategy will be expressed as costs per live birth. The incremental cost-effectiveness ratio (ICER), reflecting the extra costs required to obtain one additional live birth of each individualized treatment option compared to CC alone will be estimated as the ratio between difference in costs between strategies and the difference in pregnancy rates. A decision model will be used to evaluate the optimal strategy when also taking into account differences in multiple pregnancies, where the relative importance of different outcomes can be varied in order to evaluate whether this affects the results.

Robustness of the results (costs and health outcomes) for various assumptions and parameter estimates will be explored in sensitivity analyses and visualized in ICER-graphs and cost-effectiveness acceptability curves. In the economic analyses, we will also explore differences in patient characteristics (e.g. age, parity, ethnicity), as both costs as well as the treatment effect might differ between various groups.

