## Objective

Our primary objective is to evaluate four treatment regimens in women with WHO type II anovulation that failed to conceive after six ovulatory cycles with CC in terms of singleton live birth. Secondary objectives are to assess the safety and cost-effectiveness for these treatment regimens and to optimise guideline recommendations.

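### The ICER is defined per additional live birth but calculated with a difference in pregnancy rates, while the economic primary outcome is a third unit, singleton live birth

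*Protocol article*

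**What the plan says.** Four statements in the protocol article bear on the unit of effect.

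- Objective: the four regimens are to be evaluated "in terms of singleton live birth". Cost-effectiveness is a secondary objective.
- Economic evaluation: a cost-effectiveness analysis "with the costs per singleton pregnancy within eight months after randomisation resulting in live birth as the primary outcome measure".
- Cost-effectiveness analysis, first sentence: "Cost-effectiveness of each strategy will be expressed as costs per live birth". There is no singleton restriction here.
- Cost-effectiveness analysis, next sentence: the ICER is described as "reflecting the extra costs required to obtain one additional live birth of each individualized treatment option compared to CC alone", and it "will be estimated as the ratio between difference in costs between strategies and the difference in pregnancy rates".

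The list of secondary outcomes treats clinical pregnancy, miscarriage and multiple pregnancy as separate measures, so the protocol itself distinguishes a pregnancy from a live birth and a singleton from a multiple.

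**The concern.** Two consecutive sections use three denominators: singleton live birth, any live birth and pregnancy. The last two appear in the same sentence, one as the definition and one as the formula. A pregnancy rate counts a pregnancy that later miscarries as a success, so the formula does not return the cost of an additional live birth. It also gives a multiple pregnancy full credit, which the singleton outcome in the Economic evaluation section rules out. That matters here because the Discussion expects more multiples with gonadotrophins.

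An analyst who follows the formula would report a figure labelled cost per live birth that is something else. If the unit is left open until the data are in, it can be chosen with the results in view.

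**Working it through.** The documents state no ICER and no pregnancy rate, so there is no published figure to reproduce. The check asks how far the choice of denominator alone moves the ratio.

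**Inputs from the protocol article**
- Live birth rates from the Power calculation: 40% after CC, 55% after gonadotrophins. The 40% is taken here as the rate on CC alone.
- Cost difference from the Discussion: about 750 euro between CC and gonadotrophins. The text does not say whether this is per cycle or per course, so the euro results are illustrative. The ratios between them do not depend on it.

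**Assumed inputs**
- r, the share of pregnancies that end in live birth, so that pregnancy rate = live birth rate / r.
- The share of live births that are multiples.

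**Step 1. ICER as defined (per live birth).** 750 / (0.55 − 0.40) = 750 / 0.15 = 5,000 euro.

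**Step 2. ICER as calculated (per pregnancy), same r in both arms.** The denominator is 0.15 / r, so the result is r × 5,000.
- r = 0.9: 750 / 0.1667 = 4,500 euro
- r = 0.8: 750 / 0.1875 = 4,000 euro
- r = 0.7: 750 / 0.2143 = 3,500 euro

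The written formula is then too low by the fraction 1 − r.

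**Step 3. Different r by arm.** The denominator is 0.55 / r(other) − 0.40 / r(CC).
- r(CC) = 0.85, r(other) = 0.75: 0.7333 − 0.4706 = 0.2627, giving 2,854 euro (too low)
- r(CC) = 0.75, r(other) = 0.85: 0.6471 − 0.5333 = 0.1137, giving 6,595 euro (too high)

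The direction changes where 0.55 / r(other) − 0.40 / r(CC) = 0.15. With r(CC) = 0.80, r(other) = 0.55 / (0.15 + 0.50) = 0.846. Above that value the pregnancy-based ratio exceeds the live-birth ratio.

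**Step 4. Singleton live birth as denominator.** Assume 2% of live births on CC are multiples, and 5% or 10% on gonadotrophins.
- 5%: 0.55 × 0.95 − 0.40 × 0.98 = 0.5225 − 0.3920 = 0.1305, giving 5,747 euro
- 10%: 0.55 × 0.90 − 0.40 × 0.98 = 0.4950 − 0.3920 = 0.1030, giving 7,282 euro

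Under these assumptions, with r = 0.8 in both arms for the first, the same trial result reads as 4,000, 5,000 or 5,747 to 7,282 euro depending on which of the three units is used.

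**The case against.** The strongest reply is that the pregnancy wording is loose drafting. The same sentence speaks of an additional live birth, the sentence before it of cost per live birth, and the Economic evaluation section of pregnancies that result in live birth. The Primary outcome measure section even defines live birth through an ongoing pregnancy beyond 24 weeks. This reading is plausible, but the text does not state it, and it still leaves singleton against any live birth unresolved.

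A second reply concerns multiples. A per-woman live birth rate also counts a twin birth as one success, so changing pregnancy to live birth would not remove that problem; only the singleton restriction does. The plan also deals with multiples elsewhere: "A decision model will be used to evaluate the optimal strategy when also taking into account differences in multiple pregnancies". Both points stand, but the decision model does not correct the stated ICER formula.

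Two stronger readings are tempting. A reader might infer that the formula necessarily understates the cost per live birth. Step 3 shows that this depends on how the live-birth share differs between arms, and the documents give no shares.

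A reader might also infer, from the comparison of "the addition of IUI, use of gonadotrophins or the combination of both as compared to CC alone", that a dominated strategy would be presented as acceptable. The arithmetic is possible. Take hypothetical strategies A (+500 euro, +15 points) and B (+750 euro, +12 points): against CC alone they give 500 / 0.15 = 3,333 and 750 / 0.12 = 6,250 euro, although A dominates B. But the common comparator applies to the ICER, not to the whole evaluation, which also plans a decision model for the optimal strategy and acceptability curves. A full incremental analysis among non-dominated strategies is detail that an article may leave to the full plan, so its absence is not a defect.

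**Conclusion.** The inconsistency is real and is wrong as written: the formula does not estimate the quantity that the same sentence defines, and neither matches the economic primary outcome.

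The effect is a misstatement whose direction the documents do not fix. If the live-birth share is similar across arms, the ratio is too low by about one minus that share, for example 4,000 against 5,000 euro at 80%. It can be too high if the share is sufficiently higher in the non-CC arm. The euro values rest on the planning rates, on a 750 euro difference whose basis is not stated, and on assumed shares.

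Cost-effectiveness is a secondary objective. Randomisation and the clinical comparison are unaffected, so this should be corrected before the economic analysis but is not a must-fix for the trial.

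**What to change.** In the Cost-effectiveness analysis section, replace the difference in pregnancy rates with the difference in the proportion of women who have a singleton live birth from a pregnancy established within eight months of randomisation. Use that unit throughout this section and the Economic evaluation section, so that both agree with the Objective. Report any live birth as a sensitivity analysis.

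Optionally, report ICERs between successive non-dominated strategies alongside the ratios against CC alone; this would fit the planned decision model.

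The cost is a wording change and, for the optional part, a little extra analysis. Births and multiple pregnancies are already being recorded, so no new data are needed.

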### Power calculation

The analysis will be by intention to treat. Two comparisons will be made, one in which CC is compared to gonadotrophins and one in which the addition of IUI is compared to ovulation induction only. Assuming a live birth rate of 40% after CC, 55% after addition of IUI and 55% after ovulation induction with gonadotrophins, with an alpha of 5% and a power of 80%, we need to recruit 200 women per arm (800 women in total).

An independent Data and Safety Monitoring Committee has criticized the data of the first 150 women and concluded that a sample size re-estimation should be performed after including 320 patients (i.e. 80 per arm).

## Discussion

Subfertility occurs in 15,000 new couples in The Netherlands each year. In one-third of cases (about 5,000 women) this is due to anovulation because of WHO type II anovulation or PCOS. We estimate that annually 1,500 to 2,000 women will not have conceived after six cycles of CC, despite regular ovulation.

For women ovulating on CC but failing to conceive, no consensus exists on the optimal policy. All trials, randomised or not, have been directed at therapy naïve women, or at women with WHO type II anovulation or PCOS who remained anovulatory after CC, also called CC-resistant women. Women with who actually do ovulate on CC but do not conceive represent a larger group than CC-resistant women but have never been the focus of clinical trials. Guidelines do not indicate the optimal duration of treatment because randomised controlled trials have not been performed. As a consequence, there is large practice variation on the subject. Whereas some clinicians switch to ovulation induction with gonadotrophins with or without IUI, others continue CC treatment with IUI instead of intercourse.

There are theoretically 4 treatment options that differ in working mechanism, costs and treatment burden.

IUI is an alternative to intercourse, because it bypasses the cervical barrier, optimises timing and shortens the distance from spermatozoa to oocyt. However, IUI is much more expensive than intercourse; because sperm needs to be processed and extra hospital visits are needed. Compared to ovulation induction with clomiphene citrate, gonadotrophins require frequent subcutaneous injections and frequent clinical visits due to necessarity of close sonographic monitoring, and carry a higher risk of multiple gestations. Ovulation induction with CC will on average be about 750 euro less expensive than ovulation induction with gonadotrophins.

Discontinuing CC and starting ovulation induction with gonadotrophins and/or IUI should only be done if the probability of conception is improved or the time to conception reduced. There is a strong need for a large, randomised study that compares costs and effects of CC and gonadotrophins with or without IUI. The results of the M-OVIN study will help to make evidence-based guidelines for treatment in women with WHO type II anovulation with CC-failure.
